## Abstract

**Background:**

Treatment of patients with recurrent glioma includes neurosurgical resection, chemotherapy, or radiation therapy. In most cases, a full course of radiotherapy has been applied after primary diagnosis, therefore application of re-irradiation has to be applied cauteously. With modern precision photon techniques such as fractionated stereotactic radiotherapy (FSRT), a second course of radiotherapy is safe and effective and leads to survival times of 22, 16 and 8 months for recurrent WHO grade II, III and IV gliomas.

Carbon ions offer physical and biological characteristics. Due to their inverted dose profile and the high local dose deposition within the Bragg peak precise dose application and sparing of normal tissue is possible. Moreover, in comparison to photons, carbon ions offer an increased relative biological effectiveness (RBE), which can be calculated between 2 and 5 depending on the GBM cell line as well as the endpoint analyzed. Protons, however, offer an RBE which is comparable to photons.

First Japanese Data on the evaluation of carbon ion radiation therapy for the treatment of primary high-grade gliomas showed promising results in a small and heterogeneous patient collective.

**Methods Design:**

In the current Phase I/II-CINDERELLA-trial re-irradiation using carbon ions will be compared to FSRT applied to the area of contrast enhancement representing high-grade tumor areas in patients with recurrent gliomas. Within the Phase I Part of the trial, the Recommended Dose (RD) of carbon ion radiotherapy will be determined in a dose escalation scheme. In the subsequent randomized Phase II part, the RD will be evaluated in the experimental arm, compared to the standard arm, FSRT with a total dose of 36 Gy in single doses of 2 Gy.

Primary endpoint of the Phase I part is toxicity. Primary endpoint of the randomized part II is survival after re-irradiation at 12 months, secondary endpoint is progression-free survival.

**Discussion:**

The Cinderella trial is the first study to evaluate carbon ion radiotherapy for recurrent gliomas, and to compare this treatment to photon FSRT in a randomized setting using an ion beam delivered by intensity modulated rasterscanning.

**Trial Registration:**

NCT01166308

## Background

Recurrent gliomas remain a major challenge in radiation oncology. In the past, second courses of radiotherapy have only been applied reluctantly, in fear of treatment-related side effects. However, modern radiation techniques have enabled the radiation oncologist to deliver high local doses as an effective salvage treatment with low rates of side effects.

Especially for GBM, with unsatisfactory outcomes even after extensive research over the past centuries, effective treatment at tumor recurrence are needed urgently. With surgery and supportive care alone, overall survival is about 3-5 months. Postoperative RT can increase overall survival to 9-12 months [1]. A number of studies have shown that an additional treatment with chemotherapy can increase overall survival. This benefit, however, is commonly associated with a high risk of treatment-related side effects, especially with combination treatments, such as PCV, and with BCNU. Only recently, significant increase in overall survival could be achieved by adding TMZ, an orally applicable alkylating substance, to postoperative radiotherapy. In a prospective randomized Phase III study performed by the EORTC radiochemotherapy with TMZ was compared to postoperative radiation alone. Overall survival could be increased from 12.1 months to 14.6 months, with acceptable toxicity. TMZ was applied in a dose of 75 mg/m^2^/die during radiotherapy, followed by 6 cycles of adjuvant TMZ [2]. Therefore, standard treatment of patients with GBM is currently considered to be postoperative radiochemotherapy with TMZ, followed by 6 cycles or adjuvant TMZ.

However, with an overall survival of about 15 months, treatment outcome still remains insufficient, and patients develop tumor recurrences soon after primary diagnosis.

For anaplastic gliomas, overall survival after standard treatment following primary diagnosis, including neurosurgical resection and postoperative radiotherapy, lies between 18 and 50 months [3]. However, also these patients develop tumor recurrences after primary diagnosis, and effective salvage treatments are required.

Treatment of low grade gliomas has been discussed controversially over the last years with respect to optimal radiation dose and time point of radiotherapy. It has been shown, that doses of 45-54 Gy are sufficient for long-term local tumor control, and that early application of radiotherapy can increase progression-free survival significantly, without altering overall survival as compared to treatment applied for tumor progression [4]. During follow-up, patients develop not only low grade tumor progression, but also high-grade malignant tumor lesions.

In the past, a second course of radiotherapy has been applied reluctantly with conventional techniques as treatment outcome outweighs the risk of treatment-related side effects [5]. With modern high-precision stereotactic photon techniques, such as Fractionated Stereotactic Radiotherapy (FSRT) re-irradiation could be established as a safe and effective treatment option for recurrent gliomas [6]. Survival times of 111, 50 and 21 months for WHO Grade II, III and IV gliomas could be shown with FSRT, with very low rates of side effects. However, outcome still remains unsatisfactory [7].

Charged particles provide the physical advantage of an inverted dose profile which enables steep dose gradients. Neighboring organs at risk and surrounding normal tissue can be spared from radiation doses. Additionally, heavy charged particles, such as carbon ions, as high-LET beams, are characterized by an enhanced RBE. For glioblastoma cell lines, RBE values between 2 and 5 have been reported depending on cell line and endpoint [8,9].

In general, GBM are treatment-resistant tumors. Early studies using a high-dose proton boost could show that total doses up to 90 Gy E were effective in preventing local tumor recurrences, however, such high doses were associated with high rates of side effects [10]. Therefore, in general, standard radiation therapy is applied up to a total dose of 60 Gy. Besides the physical advantages of high local dose deposition provided by protons, carbon ions are a promising treatment alternative due to their biological benefits. A clinical study performed by the National Institute of Radiological Sciences (NIRS) treated 48 patients with malignant gliomas with a carbon ion boost up to total doses of 24.8 Gy E, of which 32 were GBM [11]. In this study, no treatment related toxicity exceeding CTCAE Grade II or higher were observed. Therefore, the concept of a carbon ion radiotherapy for the treatment of recurrent gliomas with contrast enhancing lesions is a promising treatment alternative.

Carbon ion radiotherapy was available by the Department of Radiation Oncology at the Gesellschaft für Schwerionenforschung (GSI) in Darmstadt since 1997. Superior treatment results for a number of tumor entities, such as chordomas and chondrosarcomas of the skull base, as well as ACC have been shown, and carbon ion radiotherapy is currently performed in the clinical routine for these patients [12,13]. Safety of carbon ion radiotherapy with respect to critical organs at risk, such as the brain, brainstem or spinal chord, have been shown in these studies. At the Heidelberg Ion Therapy Center (HIT), treatment of over 1300 patients per year with Proton and Carbon ion RT is possible.

*In vitro *data for the treatment of GBM with carbon ions have shown superior effectivity compared to photons [14]. Our own data have shown a high RBE for carbon ion RT for GBM; additionally a combination of carbon ion radiotherapy and TMZ have been evaluated and show an additive effect in GBM-cell lines [8]. A first clinical study evaluating a carbon ion boost in patients with GBM was recently published by Mizoe et al. [15]. Median overall survival in patients with glioblastoma was 17 months; however, only small patient numbers were evaluated and standard chemotherapy with TMZ was not applied. In that study, the carbon ion boost was applied with increasing total doses up to 24.8 Gy E. While toxicity was low even in the high dose arm, the data showed that patients seem to benefit from the high dose carbon ion boost.

The promising results in primary GBM and the known physical and biological properties of carbon ion offer a promising treatment alternative that should be evaluated for the treatment of patients with recurrent gliomas.

In the present CINDERELLA trial, the impact of carbon ion radiotherapy using intensity modulated rasterscanning will be compared to FSRT which is considered the treatment standard alternative for patients with recurrent gliomas. In a first Phase I design, the RD of carbon ion radiotherapy for re-irradiation of gliomas will be determined. In the following Phase II part, the RD of carbon ions will be compared to standard photon radiotherapy delivered as FSRT,

## Methods and Design

### Study design

The trial will be performed as a single-center two-armed randomized Phase I/II study.

#### Phase I: Dose Escalation

Patients fulfilling the inclusion criteria will be treated with increasing total doses of carbon ion radiotherapy to RD of carbon ion radiotherapy for re-irradiation of recurrent gliomas.

Patients will be treated within seven increasing dose regimens starting at 10 × 3 GyE up to 16 × 3 GyE.

#### Phase II: Randomized Part

Patients fulfilling the inclusion criteria will be randomized into two arms:

Arm A - Experimental Arm

Carbon Ion Radiation Therapy

The total dose applied will be the RD determined in the Phase I part of the study protocol.

Arm B - Standard Arm

Fractionated Stereotactic Radiotherapy with Photons

Total Dose 36 Gy, 18 fractions, 2 Gy single dose

A flow chart of the study is shown in Fig. 1.

**Figure 1 F1:**
[figure not shown]
**Flow Chart of the Cinderella-Study**.

### Study objectives

The purpose of the trial is to compare carbon ion radiotherapy to FSRT for the treatment of recurrent gliomas delivered to the area of contrast-enhancement in T1-weighted MRI and/or Amino-Acid-PET-positive lesions.

In the Phase I study, the RD of carbon ion radiotherapy will be determined in a dose escalation scheme. The primary endpoint is toxicity.

In the randomized Phase II part of the study, carbon ion radiotherapy treated at the recommended dose evaluated in the phase I part will be compared to standard photon radiotherapy delivered as FSRT. The primary endpoint is survival after re-irradiation at 12 months.

### Primary Objectives

#### Phase I

The primary objective is any Grade IV toxicity related to the study treatment according to CTCAE Grade IV.

#### Phase II

The primary objective is survival after re-irradiation at 12 months.

### Secondary Objectives

#### Phase I

The secondary objective in the Phase I part is survival after re-irradiation

#### Phase II

The secondary objectives of the study are progression-free survival, toxicity and safety.

### Patient selection: Inclusion criteria

Patients meeting all of the following criteria will be considered for admission to the trial:

- unifocal, supratentorial recurrent glioma (primary histologies including any WHO Grade II or III glioma or glioblastoma)

- prior course of standard photon radiotherapy

- contrast enhancement on T1-weighted MRI and/or Amino-Acid-PET-positive high-grade tumor areas

- indication re-irradiation

- age ≥ 18 years of age

- Karnofsky Performance Score ≥60

- For women with childbearing potential, (and men) adequate contraception.

- Ability of subject to understand character and individual consequences of the clinical trial

- Written informed consent (must be available before enrolment in the trial)

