### Patient selection: Exclusion criteria

Patients presenting with any of the following criteria will not be included in the trial:

- Multifocal Glioma or Gliomatosis cerebri

- refusal of the patients to take part in the study

- previous re-irradiation or prior radiosurgery or prior treatment with interstitial radioactive seeds

- time interval of < 6 months after primary radiotherapy

- Patients who have not yet recovered from acute toxicities of prior therapies

- Known carcinoma < 5 years ago (excluding Carcinoma in situ of the cervix, basal cell carcinoma, squamous cell carcinoma of the skin) requiring immediate treatment interfering with study therapy

- Pregnant or lactating women

- Participation in another clinical study or observation period of competing trials, respectively.

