#### Phase II

• The size of the phase II part of this study is determined by the primary aim of testing experimental treatment for superiority over standard treatment. This endpoint is a censored failure time.

• Information on the OS_B__12mR (overall survival rate after 12 months of follow-up for standard treatment) is given in literature data [17].

To calculate survival data, a population distribution of GBM in 34.3%, Grade III Tumors in 24.4% and low grade gliomas in 41.3% was used [17]. Survival rates for overall survival were taken as published previously with 23% for GBM 65% for Grade III, and 77% for low-grade gliomas observed at 12 months after re-irradiation [17].

Overall OS_B__12mR can be calculated as weighted mean rate. Therefore OS_B__12mR is expected to be 56%. The study will be designed to detect an improvement in OS_12mR of 10% (OS_A__12mR = 66%).

The statistical error rates for this test of superiority are set as α = 0.05 and β = 0.20 (power 80%). Sample size calculation is based on an unstratified log-rank. It can be expected that including histology in a stratified log-rank test will increase the power as compared to the unstratified test.

The recruitment period will be 36 months with a minimal follow-up time of 12 months. In order to put more patients on the experimental treatment, an unbalanced randomization allocation ratio of 2:3 was chosen.

For this set of assumptions, the sample size calculation programme PASS 2008 yields the total sample size for standard treatment of n = 138 and n = 207 for experimental treatment. Allowing for failures for various reasons of 10%, a total of N = 380 is required for this part of the study (n = 152 in standard arm and n = 228 in experimental arm). Patients will be stratified by histology.

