#### Phase II

##### Primary endpoint

The primary endpoint variable OS_12 m was planned to be analysed by a one sided logrank test of stratified by histology testing H_0_: OS_A_-12 m = OS_B_-12 m versus H_1_: OS_A_-12 m > OS_B_-12 m at the level of alpha = 5%. One interim analysis is planned when 50% of the number of expected events under the null-hypothesis have occurred. In order to preserve the significance level of 5% a sequential plan with alpha-spending of De-Mets and Lan with limits of O'Brien and Fleming is applied.

Overall survival will be summarized by Kaplan-Meier curves. Median estimates as well as associated 95% confidence intervals will be reported. Further, a descriptive analysis of the primary outcome variable is performed applying a Cox-regression model.

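### The confirmatory survival test uses histology alone; prespecified adjustment for Karnofsky score, age and interval since first radiotherapy, all known at entry, could add power at no patient cost

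*Protocol article*

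**What the plan says.** The inclusion criteria require "Karnofsky Performance Score ≥60" and an age of at least 18 years. The exclusion criteria rule out patients with a "time interval of < 6 months after primary radiotherapy". Under Statistical Methods, Phase II, the primary endpoint "was planned to be analysed by a one sided logrank test of stratified by histology", at a level of 5%. The same section adds that "a descriptive analysis of the primary outcome variable is performed applying a Cox-regression model", and names no covariates for it.

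Sample Size Calculation, Phase II, bases N on an unstratified log-rank test and then remarks: "It can be expected that including histology in a stratified log-rank test will increase the power as compared to the unstratified test". Histology is also the randomisation stratum. It is the only factor for which the document gives survival figures.

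**The concern.** Nobody can be enrolled without a Karnofsky score, an age and an interval since first radiotherapy. These values are therefore complete and fixed before allocation. None of the three criteria sets an upper limit, so patients within one histology stratum can differ widely on all of them.

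Where such values carry prognosis, leaving them out of a survival analysis pulls the estimated treatment effect toward no difference and lowers power. Adjusting for them recovers that power with the same patients, follow-up and error rate. The protocol uses this reasoning for histology and stops there.

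The choice is not simply left to a later SAP. The protocol names the decisive test and gives the regression a descriptive role, so an SAP could not make an adjusted test decisive without amending the protocol. At stake is a possible gain in the chance of detecting the planned 10-point difference.

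**Working it through.** **Inputs from Sample Size Calculation, Phase II.** Histology mix 34.3 / 24.4 / 41.3% (GBM, grade III, low grade); 12-month survival 23 / 65 / 77%; target 56% v 66%; 36 months of recruitment plus at least 12 months of follow-up; allocation 138:207 (40% standard); power 80%. The one-sided 5% level is from Statistical Methods.

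**1. The plan's own figures.**
- Control rate: 0.343 × 23 + 0.244 × 65 + 0.413 × 77 = 7.889 + 15.860 + 31.801 = 55.55%, stated as 56%.
- Hazard ratio implied by the overall rates: ln 0.66 / ln 0.56 = 0.717.
- Events (Schoenfeld): (1.645 + 0.842)² / [0.4 × 0.6 × (ln 0.717)²], rounded up, = 233.
- Event probability per arm, with λ = −ln(S₁₂)/12: 1 − (e^(−12λ) − e^(−48λ))/(36λ) = 0.735 (standard) and 0.623 (experimental). Mean: 0.4 × 0.735 + 0.6 × 0.623 = 0.668.
- N = 233 / 0.668 ≈ 349, against 345 stated. Power at 345 is 79.7%. The plan's figure reproduces.

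**2. Treatment effect within histology.** To bring overall carbon survival to 66% with a common hazard ratio in all strata, that ratio must be about 0.663: 0.343 × 0.23^0.663 + 0.244 × 0.65^0.663 + 0.413 × 0.77^0.663 = 0.129 + 0.183 + 0.347 ≈ 0.66. This is stronger than 0.717 because the overall ratio is diluted by mixing histologies.

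**3. Assumption not in the document.** Let s be the SD of the log hazard explained jointly by the three entry values within a stratum. The document gives no value, so a range is shown. As a benchmark, the stated rates imply an SD of about 0.76 for histology itself (weighted SD of the log of −ln 0.23, −ln 0.65, −ln 0.77).

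**4. Simulation.** 5000 trials per cell, N = 345, 60% on carbon ions, exponential survival given a normal prognostic index, stratum rates held at 23 / 65 / 77% on standard treatment, treatment ratio set to give 66% overall on carbon ions, critical value 1.645.

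| s (assumed) | Ratio giving 66% | Log-rank stratified by histology | Stratified Cox, adjusted | Gain (points) |
|---|---|---|---|---|
| 0 | 0.663 | 90% | 90% | 0 |
| 0.3 | 0.654 | 89% | 91% | 2 |
| 0.5 | 0.639 | 88% | 93% | 5 |
| 0.7 | 0.618 | 86% | 95% | 9 |

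Type I error was 4.7 to 5.4% for both tests.

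**5. Cross-checks.**
- A separate simulation with 3000 trials per cell gave 90.7 v 90.5% at s = 0, 87.1 v 91.7% at 0.4 and 86.9 v 94.2% at 0.6. An unstratified test had about 72 to 75% power there, so histology stratification already supplies most of the available gain.
- Estimating three separate coefficients (equal, independent contributions; 2000 trials per cell) gave 89 v 89% at s = 0, 88 v 91% at 0.3, 88 v 94% at 0.5 and 87 v 96% at 0.7. Type I error was 4.4 to 6.6%, and the two tests differed by no more than 0.8 points in any cell.
- Adding strata (histology × thirds of the index) is a poorer route: at s = 0 power went from 89.8 to 88.5%.

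**The case against.** The strongest reply is that nothing in the plan is wrong. A log-rank test stratified by the one factor with documented prognostic strength is valid and accepted, and the remark on power in the sample-size section claims a gain only for the factor it has data on. This stands.

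Three stronger readings are tempting, and the document supports none of them.

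- *The trial is losing power.* Wide eligibility shows a range of values, not that those values predict survival within histology. The document gives no survival figure by Karnofsky score, age or interval. The loss is conditional on s being above zero.
- *The trial needs this change.* At the planned effect the histology-stratified test has about 86 to 90% power across the range, above the 80% target. N was set on an unstratified test, so a reserve is built in.
- *Power falls below 80%.* A reader who applies the ratio 0.717 within strata will find this (76% at s = 0). But 0.717 comes from the overall rates. Within histology it gives carbon survival of 0.343 × 0.23^0.717 + 0.244 × 0.65^0.717 + 0.413 × 0.77^0.717 ≈ 64.1%, a difference of 8.6 points, shrinking to 7.4 points at s = 0.7. That is a smaller effect than the 10 points planned, so it does not show a shortfall at the planned effect.

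It is also fair to say that the simulated gains are favourable for each s. The covariates were measured without error and entered in the correct form, and no interim look was modelled. The proposed linear and log forms may fit less well, which would reduce the gain.

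**Conclusion.** The point holds as an optional efficiency improvement. The confirmatory test ignores three values that are complete at entry, and the protocol fixes this choice. If the values carry no prognosis within histology, nothing material is lost or gained by adjusting. If they are mildly to strongly prognostic (s from 0.3 to 0.7, all below histology's own 0.76), adjustment adds about 2 to 9 points of power at the planned effect, with type I error close to 5%. The plan is neither in error nor underpowered on this account.

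The size rests on an assumed s, exponential survival, a proportional effect common to all histologies, and a single final look at one-sided 5%. At the stated final level of 0.042, power would be slightly lower for every test.

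**What to change.** Before any outcome data are seen, amend the Phase II primary-endpoint paragraph under Statistical Methods:

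- Make the primary one-sided test the treatment test in a Cox model stratified by histology and adjusted for baseline Karnofsky score (linear), age (linear) and log interval since primary radiotherapy, all as recorded before randomisation.
- Use that same test, with the same alpha-spending, at the interim and final analyses.
- Report its hazard ratio and confidence interval as the main effect estimate.
- Keep the histology-stratified log-rank test as a named sensitivity analysis.

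The cost is wording only: no extra patients, visits or data, and N stays as it is. There are two small downsides. The hazard ratio becomes conditional on the covariates, and the test relies on a working covariate model; the log-rank sensitivity analysis covers the latter. Keeping the current test is also defensible.

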### Patient selection: Exclusion criteria

Patients presenting with any of the following criteria will not be included in the trial:

- Multifocal Glioma or Gliomatosis cerebri

- refusal of the patients to take part in the study

- previous re-irradiation or prior radiosurgery or prior treatment with interstitial radioactive seeds

- time interval of < 6 months after primary radiotherapy

- Patients who have not yet recovered from acute toxicities of prior therapies

- Known carcinoma < 5 years ago (excluding Carcinoma in situ of the cervix, basal cell carcinoma, squamous cell carcinoma of the skin) requiring immediate treatment interfering with study therapy

- Pregnant or lactating women

- Participation in another clinical study or observation period of competing trials, respectively.

